# Influence of digital media in the oral health education of mother-child pairs: study protocol of a parallel double-blind randomized clinical trial

**DOI:** 10.1186/s13063-022-06602-4

**Published:** 2022-08-09

**Keywords:** Dental caries, Oral health, Digital media, Mother, Child

## Abstract

**Background:**

Dental caries is the most common non transmissible chronic disease in childhood and the control of dental biofilm in children is one of the greatest challenges in oral disease prevention. Digital media applications can help patients in improving their oral hygiene performance and reducing the number of appointments due to pain and discomfort reasons. This study aims to investigate the use of an smartphone application (WhatsApp) to deliver oral health education to mother-child pairs, with the ultimate goal of controlling dental biofilm and caries through digital activities focused on oral hygiene.

**Methods:**

This study was designed as a randomized, double-blind, parallel clinical trial involving 100 pairs of mothers and children (6–12 years old). The mothers and children will be randomly allocated to the control group (*n* = 50 pairs), who will receive a single visit conventional oral health education, or to the experimental group (*n* = 50 pairs), who will receive both a single visit conventional oral health education and educational videos through WhatsApp Messenger, twice a week. Before randomization of the groups and after the intervention, pairs will be evaluated regarding to plaque index (VPI), gingival bleeding index (GBI), and number of decayed, missing and filled permanent or primary teeth (DMF-T) modified by the inclusion of active non-cavitated carious lesions (Nyvad criteria). Socioeconomic data, dental history, and oral health literacy will obtained using questionnaires (Oral Health Literacy Assessment Task for Paediatric Dentistry; BOHLAT-P). Chi-square, Student’s *t*-test, paired Student’s *t*-test, Mann-Whitney, and Friedman tests will be used with a 5% significance level.

**Discussion:**

This intervention proposal is designed to motivate behavioral change in mother-child pairs. We hypothesize that adding digital media to traditional oral health programs will provoke improvements in oral hygiene behavior and health outcomes. To our knowledge, this is the first study evaluating the effect of educational videos communicated by digital media (WhatsApp) on the oral health of mother-child pairs evaluated by long-term dental examinations. In addition, we will assess the maternal level of comprehension of the provided information via a literacy assessment tool. The clinical trial is registered at the Brazilian Registry of Clinical Trials (No. RBR-7s8bw6m).

**Supplementary Information:**

The online version contains supplementary material available at 10.1186/s13063-022-06602-4.

## Background

Dental caries is the most common non transmissible chronic disease in childhood and a major public health problem worldwide [1–3]. One of the greatest challenges in oral disease prevention is the control of dental biofilms and gingival inflammation in children [4, 5]. Because prevention plays a crucial role in reducing oral health problems [6], adequate oral care, including dental flossing, brushing, and diet control (in particular, reducing sugar intake) should be initiated on the eruption of the first teeth, as an effective strategy to prevent oral diseases [5, 7–9]. Early education is the basis for desirable habits and behaviors as well as for effective lifestyle changes in the future [10].

Dentists and dental teams are critical for early oral health education. Because they have theoretical and practical knowledge as well as the required training, dental teams play an essential motivational role in the practice and maintenance of good oral hygiene and the modification of poor habits [11–13]. The World Health Organization recommends that interventions involving oral health education be associated with other health promotional activities, particularly the development of healthy habits [14]. The existing literature suggests various methods for the promotion of oral health, education, and motivation including direct orientation, videos, leaflets, substances evidencing bacterial plaque, lectures, puppets, gymkhanas, theater, and music, among others [15–17].

Digital media such as the Internet, together with health organizations, also plays an important role in providing education, motivation, and information [18]. Since 2014, more than 50% of adults have searched for health information on the Internet [19]. Also,  previous study demonstrated that between 2016 and 2018, more than half of adults (50.4%) and children (58.8%) accessed primary dental care information via the Internet [20]. With the advancement of the Internet, numerous social media platforms have become available for personal interaction and information searches. To date, social media platforms have been used more frequently than traditional search engines [21].

Dental studies have achieved good results using an oral health education tool to inform and motivate adolescents [22, 23]. A digital medium with widespread use in Brazil is WhatsApp Messenger, which is an application that allows rapid interaction through texts, images, voice and video calls [24]. Consequently, this application may be an effective social media tool for disseminating health education [25]. In this context, a 2016 survey conducted in Brazil showed that 76% of users who searched the Internet made continuous use of WhatsApp, and this percentage is one of the highest worldwide, second only to South Africa [26]. However, the efficacy of using WhatsApp to promote oral health education for mothers and children has not yet been elucidated in the literature.

The objective of this parallel, double-blind, and randomized clinical trial is to compare the influence of conventional education promoting oral health, versus that of conventional education plus the WhatsApp digital platform, in controlling dental biofilm and caries in mother-child pairs. Mothers and their children (age 6–12 years) will be evaluated through a self-administered questionnaire on oral hygiene habits, and through the Oral Health Literacy Assessment Task for Paediatric Dentistry (BOHLAT-P). In addition, clinical parameters of the mother-child pairs (including the visible plaque index [VPI], gingival bleeding index [GBI], number of decayed, missing, and filled deciduous teeth [dmft], and the numbers of decayed, missing, and filled permanent teeth [DMFT modified by the inclusion of active non-cavitated carious lesions]) will be considered in the assessment. We hypothesized that mother-child pairs randomized to the experimental group would exhibit greater improvements in oral hygiene behavior and health outcomes when compared with the control group during follow-up assessments at 1, 6, and 12 months.

## Materials and methods

### Ethics approval and consent to participate

This clinical trial was approved by the Committee for Ethics in Research Involving Human Beings (CAAE: 50783521.9.0000.5419) and is outlined according to CONSORT recommendations. The trial has been registered with the Brazilian Registry of Clinical Trials (# RBR-7s8bw6m).

### Study design

This study is a randomized, double-blind, parallel clinical trial with voluntary participation and 12 months of follow-up. The protocol follows the recommendations of the 2013 interventional trials (SPIRIT) guidelines.

### Sample size and power calculation

To calculate the sample size, we used the study by Zolfaghari et al. [10], which measured the efficacy of a game for delivering oral health knowledge to children and mothers. Considering an alpha value of 5% and a test power of 80%, the sample calculation requirement was 44 mother-child pairs per group (control and experimental).

### Participants and study setting

After anamnesis and initial clinical examination, the dental examination will be performed at the Clinical Research Center at the School of Dentistry of Ribeirão Preto at University of São Paulo, Brazil (FORP/USP). Once the study details are explained and queries are addressed, volunteers (mothers) are expected to sign the informed consent form (TCLE), and the children are expected to sign the assent form.

### Inclusion criteria

All mothers have to be at least 18 years old

Children (6–12 years old) of both sexes

Participants (mother-child pairs) with good general health (reported by the mother)

Mothers using WhatsApp Messenger on their smartphones

### Exclusion criteria

Participants (mothers and children) exhibiting learning difficulties

Mothers with total upper and lower dental prostheses

### Interventions

The following study groups will be created in parallel to evaluate the proposed intervention. (1) Control group: Both mothers and children will undergo clinical examination, prophylaxis, topical fluoride application, and oral hygiene guidance on a single dental office visit. The pairs will receive an oral hygiene in-person orientation session that will take about 30 min regarding to oral health, gingival health, sugar intake, fluoride importance in prevention of dental caries, and oral hygiene habits, complemented with illustrative resources.

(2) Experimental group: Both mothers and children will receive clinical examinations, prophylaxis, topical fluoride application, and oral hygiene guidance on a dental office visit. Additionally, the digital platform WhatsApp Messenger (Mountain View, California) will be used to provide educational videos to the mother-child pairs, twice per week (Tuesday and Thursday) at 7 PM over a period of 4 weeks. A WhatsApp video presenting a story on oral health, along with a reminder to perform their oral hygiene routine (toothbrushing and flossing) will be sent to the mother-child pairs in the experimental group. Topics including oral hygiene, dental biofilms, white spot lesions, dental caries, and the importance of dental appointments will be covered. Videos were validated by educators and a group mother-child pairs who evaluated the quality of the animated videos and understanding of the topics covered according to Marinho et al. [27].

At the end of 4 weeks (T1), 6 months (T2), and 12 months (T3), the mother-child pairs will undergo follow-up clinical evaluations at FORP/USP. If needed, dental treatment will be performed by a research team at the same institution.

Theoretical training took place for an examiner ([name]) along with the reference standard examiner ([name]) through expository classes regarding the following indexes: VPI; GBI; decayed, missing, and filled permanent teeth (DMFT); and decayed, missing, and filled primary teeth (dmft) and Nyvad criteria to assess active non-cavitated carious lesions. Oral examination of the mother-child pairs will be performed by a trained and calibrated operator ([name]) and assisted by a trained annotator ([name]). The examinations will be performed with the mother-child pairs seated in front of the examiner. The dentist will be used individual protection equipment, a sterilized flat oral mirror (Golgran, São Caetano do Sul, São Paulo, Brazil), and a sterilized periodontal probe (WHO-621, Trinity®, Campo Mourão, PA, Brazil). The visible plaque index (VPI) will be used to evaluate the mesial, distal, vestibular, and lingual surfaces of the incisors and first upper and lower molars according to the criteria set by Ainamo and Bay [28]. Evaluations will be performed by direct visualization of the vestibular and palatine/lingual surfaces. A flat oral mirror # 5 (Golgran, São Caetano do Sul, São Paulo, Brazil) will be used for the visual examination. The established scores for the VPI are (1) presence and (0) absence. For the gingival bleeding index (GBI), a periodontal probe (WHO-621, Trinity®, Campo Mourão, PA, Brazil) will be used to evaluate the subgingival surfaces 1 mm into the sulcular epithelium. The bleeding on probing index will also be recorded as (1) presence of bleeding and (0) absence of bleeding. Oral hygiene will be considered unsatisfactory if the percentage of visible biofilm is greater than 15% and/or gingivitis is present, as indicated by bleeding at more than 15% of the evaluated sites [25, 28].

After brushing, a clinical oral examination will be performed to verify the participants’ oral health condition, and the data will be recorded using the dmft and DMFT index for deciduous and permanent teeth, respectively [29, 30]. Dental caries will be evaluated using the Nyvad Criteria to assess severity and activity of carious lesions, including lesions of rough and opaque white spots [31]. The initial evaluation aims to verify the inclusion criteria for the study participants. Subsequent evaluations will aim to assess the effectiveness of the interventions for improving the oral hygiene of the mother-child pairs.

### Randomization and allocation concealment

Patients will be randomized using a simple draw. A number will be assigned to each mother-child pair. A virtual randomization program [32] will be used to generate the allocation sequence in the groups, and the names of the mother-child pairs of the randomized groups (control and experimental) will be recorded by [name] so that the clinical examiner ([name]) and the statistical evaluator ([name]) will not have access to this information. [name] will also be responsible for sending the video individually to each participant of the experimental group using the WhatsApp application. The participants will be blinded to the data collection. Both the examiner involved in the intervention and the statistician who will analyze the data through appropriate statistical tests will be blinded.

Figure 1 summarizes the study design, randomization process, group allocation, and evaluation periods.

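### The simple draw does not guarantee the stated 50 pairs per arm, and it leaves child age to chance in a comparison whose named tests do not adjust for age

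*Protocol article*

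**What the plan says.** All places are in the protocol article.

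- **Randomization and allocation concealment:** "Patients will be randomized using a simple draw". The unit is the pair: "A number will be assigned to each mother-child pair". Then: "A virtual randomization program [32] will be used to generate the allocation sequence in the groups". No block size, fixed quota, stratification factor or minimisation is named. The clinical examiner and the statistician have no access to the allocations.
- **Abstract, Methods:** a "parallel clinical trial involving 100 pairs of mothers and children (6–12 years old"), with pairs "randomly allocated to the control group (*n* = 50 pairs") and the same number in the experimental group.
- **Sample size and power calculation:** with alpha 5% and power 80%, "the sample calculation requirement was 44 mother-child pairs per group (control and experimental").
- **Inclusion criteria:** "Children (6–12 years old) of both sexes".
- **Measurement of primary outcomes:** VPI, GBI, dmft for the deciduous teeth and DMFT for the permanent teeth.
- **Baseline data:** age is collected.
- **Discussion:** caries is described as related to age.
- **Statistical analyses:** Mann-Whitney between groups and Friedman within groups for plaque and bleeding; t and chi-square tests for caries experience. No covariate is named.

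**The concern.** In ordinary trial usage a simple draw is unrestricted: each pair is allocated independently and the arm totals are random. Fixed arms of 50 are not a property of that method, so the abstract and the randomization section need to be reconciled.

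The second issue is age. Between 6 and 12 years children pass from primary to permanent teeth, so age affects which teeth can enter dmft and which can enter DMFT. The stated allocation does nothing to balance age, and the stated tests do nothing to account for it. In a trial of 100 pairs an age difference of several months between arms is quite likely. It would make a positive or a null caries result harder to interpret, and age-related variation would stay in the error term.

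**Working it through.** **Inputs from the article:** 100 pairs, 50 planned per arm, 44 required per arm, alpha 5%, power 80%, children aged 6–12.

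**Assumptions, because the article gives no figure:** two-sided test; SD of child age 2 years (1.5 also shown); age–outcome correlation 0.3 to 0.5.

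**1. The stated 44 per group.** It cannot be reproduced, because no endpoint, effect size or SD is given. Solving backwards with the two-sample normal formula, d = (1.960 + 0.842) × √(2/44) = 0.597. This is used below only as a yardstick.

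**2. Arm sizes under unrestricted 1:1 allocation.** Control-arm size X ~ Binomial(100, 0.5).
- P(X = 50) = 0.080
- P(one arm below 44) = 2 × P(X ≤ 43) = 0.193
- P(both arms between 40 and 60) = 0.965

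**3. What unequal arms cost.** Power = Φ(d / √(1/n₁ + 1/n₂) − 1.960), with d = 0.597.

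| Split | Power |
|---|---|
| 50/50 | 84.8% |
| 44/56 | 84.3% |
| 43/57 | 84.1% |
| 40/60 | 83.3% |

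Averaged over the binomial distribution, power is 84.4%, which is 0.4 points below 50/50. It falls below 80% only if the smaller arm has 32 pairs or fewer (probability 0.04%).

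**4. Chance imbalance in age.** This holds for a coin-flip draw and, in essence, for a draw of 50 numbers out of 100. The standard error of the difference in mean age with 50 per arm is SD × √(2/50) = 0.2 × SD.
- SD 2 years: SE 0.40 year, 95% range ±0.78 year. P(difference over 0.5 year) = 2 × [1 − Φ(0.5/0.40)] = 21%; P(over 1 year) = 1.2%.
- SD 1.5 years: SE 0.30 year. P(difference over 0.5 year) = 2 × [1 − Φ(0.5/0.30)] = 10%.
- If half the children are aged 6–8 (assumed), a fixed draw of 50 from 100 leaves the arms at least 15 points apart in that share in 16% of trials, and at least 20 points apart in 7% (hypergeometric).

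**5. Effect on an age-related index.** For correlation ρ, the 95% chance shift is 1.96 × ρ × √(2/50) outcome SDs.
- ρ = 0.3: 1.96 × 0.3 × 0.2 = 0.12 SD, or 20% of d = 0.597
- ρ = 0.5: 1.96 × 0.5 × 0.2 = 0.20 SD, or 33% of d

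Adjustment for age would remove ρ² of the outcome variance, that is 9% to 25%.

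**6. What a change during recruitment can achieve.** Recruitment runs from January to December 2022 and the article appeared in August. With steady accrual (assumed), about 7/12 × 100 = 58 pairs are already drawn. If those were allocated by coin flip and the other 42 split 21/21, then P(50/50 overall) = P(Binomial(58, 0.5) = 29) = 10%, and P(one arm below 44) = 2 × P(Binomial(58, 0.5) ≤ 22) = 9%.

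**The case against.** **The draw may not be unrestricted.** The article does not use that word. Numbering 100 pairs and letting a program pick 50 could also be called a simple draw, and would give exactly 50/50. This stands. A reader might infer that the method cannot deliver 50 per arm; the text supports only that it does not guarantee it. The figures in step 2 belong to one of two readings.

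**An arm below 44 hardly matters for power.** This also stands. A reader might infer that the sample-size requirement is missed in roughly one trial in five. In power terms it is not: 43/57 keeps 84%.

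**The age argument can be pushed too far.** A reader might take child age to be the main driver of the indices, or the arms to need balancing over the recruitment year. The article says only that caries is related to age, and nothing in it suggests a time trend. Child age says little about the mothers' indices. VPI is scored on selected teeth and judged as a percentage, so the tooth-count argument does not carry over to plaque and bleeding. Simple randomization of 100 pairs is valid, and its chance imbalances are already covered by the 5% error rate. What remains is that the children's dmft and DMFT are age-dependent primary measures, with neither balance nor adjustment provided for.

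**A fuller plan may hold the detail.** Strata and covariates are often left to a statistical analysis plan, so it cannot be said that nothing will correct for age. But the article does state an allocation method and does name its tests, and those can be judged as they stand.

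**Conclusion.** The point holds as something that should be changed; it does not invalidate the randomization. The stated method does not guarantee the stated arm sizes: 8% chance of 50/50 and 19% chance of an arm below 44 if the draw is unrestricted, at a power cost of under 1 percentage point. Independently of how the draw is read, child age is left to chance and the named between-arm tests ignore it. A mean age difference of more than half a year arises in 21% of trials with an age SD of 2 years, and in 10% with 1.5 years. The loss is in precision and in how readily the caries result can be interpreted, with no bias on average. The age figures rest on the assumed SDs, and the shift of 0.12 to 0.20 SD on the assumed correlations.

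**What to change.** **Allocation, for pairs not yet allocated.** Replace the simple draw with 1:1 permuted blocks of randomly varying size, stratified by child age band (6–8 and 9–12), generated by the same program and held by the same allocation holder. Keep pairs already drawn as they are, and state how they were drawn (independently, or as 50 out of 100).

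**Analysis, for all pairs.** Adjust the between-arm comparison of the children's indices for child age, which is already collected at baseline. Use regression or ANCOVA, or a rank test stratified by age band, in place of the unadjusted Mann-Whitney and t tests.

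**Reporting.** Give the arm sizes actually obtained. If the earlier draws were independent, the change cannot ensure 50 per arm (step 6).

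**Cost.** A revised sentence on allocation, a new list, and a small but real change to the named tests; no extra pairs, visits or staff. Block ends become slightly predictable to someone who knows past allocations. Varying block sizes and an examiner without access to the allocations limit this.

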### Outcome measurements

Measurements will be taken at baseline, post-intervention (i.e., 30 days after completion of the intervention), and at the 6-month and 12-month follow-up points. All follow-up assessments will be conducted by a researcher blinded to the group allocation of the participants.

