### Measurement of secondary outcomes

The secondary outcome is defined as the participant responses to the questionnaire on socioeconomic data, oral hygiene, visits to the dentist, and acceptability of the animation by the pairs mother-child. At the end of T3, the mothers of the experimental group will be asked if the videos were watched at the moment they were sent or if they was watched in other times after the intervention. Question will include how often the videos were watched, which videos they and their children liked the most, and what subject was easier or more difficult to understand and suggestions for improvement. Quality of life will be evaluated using the BOHLAT-P questionnaire [33]. This questionnaire contains 49 questions and is divided into three domains: oral health knowledge, textual understanding, and numerical skills [34]. The mother will answer the BOHLAT-P questionnaire alone, and the researchers will provide help if requested.

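### The trial is called double-blind, but the design supports only examiner and statistician blinding, and the T3 video questions cannot be put by a researcher blind to allocation

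*Protocol article*

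**What the plan says.** The title, abstract, objective and design section all use the label double-blind. Study design reads: "This study is a randomized, double-blind, parallel clinical trial with voluntary participation and 12 months of follow-up".

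Randomization and allocation concealment then deals with three parties.

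- **Participants:** "The participants will be blinded to the data collection".
- **Examiner and statistician:** "Both the examiner involved in the intervention and the statistician who will analyze the data through appropriate statistical tests will be blinded". The mechanism is given too. Another team member records the allocation, and the examiner and statistician "will not have access to this information".
- **The person holding the allocation:** this person "will also be responsible for sending the video individually to each participant of the experimental group using the WhatsApp application", and is therefore unblinded by role.

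Interventions gives controls "oral hygiene guidance on a single dental office visit". The experimental arm gets the same office care plus videos and a hygiene reminder by WhatsApp, twice weekly for 4 weeks. Under the retention strategies, both arms get appointment texts.

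Outcome measurements states: "All follow-up assessments will be conducted by a researcher blinded to the group allocation of the participants". Measurement of secondary outcomes adds that, when T3 ends, "the mothers of the experimental group will be asked if the videos were watched", with further questions on viewing frequency, preferences and comprehension.

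**The concern.** Two statements do not fit the design.

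First, the label and the sentence on participants invite the reader to believe that participants are masked. A mother who receives repeated videos on her own phone is not. Being blinded to data collection also has no workable meaning for people who are examined and who fill in questionnaires.

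Second, a researcher blind to allocation cannot carry out an assessment given to one arm only. The video questions belong to a secondary outcome, the acceptability of the animation, so the statement that all follow-up assessments are blinded cannot be true of that outcome.

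The examiner's blind carries real weight here. The primary outcome rests on VPI, GBI and the caries indices. VPI and GBI are scored as present or absent by one trained and calibrated operator, VPI by sight and GBI by probing. Calibration and fixed criteria limit random disagreement, but they do not protect against a lean towards one arm once the arm is known. Any self-reported behaviour collected after the intervention has no masking at all.

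**Working it through.** No figure in the article bears on blinding, so the check sets the sections side by side.

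**1. Can participants be blind to allocation?** From Interventions, the experimental arm receives 2 sends per week × 4 weeks = 8 sends, each with a reminder. The control arm receives none, and no sham or attention messages are described. The appointment texts go to both arms and so mask nothing. Experimental mothers therefore know they are getting the videos. What control mothers know about the other arm depends on consent wording that is not shown. Participants and study setting says only that the study is explained before signature.

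**2. What does the article claim for participants?** It claims blinding to data collection, and nowhere says in so many words that mothers are blind to allocation. The sentence does, however, place participants beside the examiner and statistician in the account of who is blinded, under a double-blind label.

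**3. Which blinding is supported?** Examiner and statistician blinding is stated, with the allocation list withheld from both. That is the only safeguard described. Nothing in the article asks pairs not to mention videos to the examiner, so conversation at T1, T2 or T3 remains a possible route of unmasking.

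**4. Can all follow-up assessments be made by a blinded researcher?** Outcome measurements says yes. Measurement of secondary outcomes directs the video questions to experimental mothers only. Anyone who asks them must know whom to ask, so the two sections conflict for this outcome.

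**5. Does that reach the clinical scores?**

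| Visit | Can the T3 video questions affect its scores? |
|---|---|
| Baseline, T1, T2 | No, already scored |
| T3, examiner neither asks nor hears them before scoring | No |
| T3, examiner asks or hears them before scoring | Yes, up to the whole experimental arm (50 pairs planned) |

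The article does not state who asks, or where the questions fall relative to T3 charting.

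**6. Is the statistician's blind affected?** Data management places all data in a spreadsheet. Items completed for one arm only would show the statistician which arm is which, unless they are held separately.

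**7. Can it still be changed?** Trials status gives first recruitment in January 2022. Adding 12 months, no T3 visit falls before January 2023. The article is dated August 2022, so as of publication the T3 order could be fixed before any T3 visit.

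**The case against.** The strongest reply is that double-blind may simply mean examiner and statistician. Both are stated to be blinded, with a mechanism, and the article never literally claims that mothers are unaware of their group. On that reading the flaw is one badly worded sentence. The reply has force. A reader might infer that no blinding exists in this trial, and the article does not support that. But the label remains ambiguous and sits beside a sentence that counts participants among the blinded, so it still needs correcting.

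Four further replies limit how far the point goes.

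- **All participants unblinded.** A reader might infer that every participant knows the allocation. This is established for experimental mothers only, because the consent text is not shown.
- **Examiner unmasked at T3.** A reader might infer this from the video questions. Their placement at the end of T3 may already mean after charting, no text says the examiner asks them, and the schedule figure is not shown. The conflict over who can ask them stands, but unmasking of the examiner is only a possibility.
- **Self-reports biased by reminders.** Questionnaires says the self-report form is applied before the interventions, and such answers cannot reflect the messages. The objective and the secondary outcomes suggest that hygiene behaviour is also an outcome, so the concern applies to whatever is collected afterwards.
- **Operational detail.** An article may leave the order of procedures to the full protocol. Silence on the order is therefore not itself the fault. The fault is the statement about all follow-up assessments, which is wrong as written.

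**Conclusion.** The point holds in limited form. Participant blinding is suggested by the label and by the sentence on participants, but the design does not provide it. Examiner and statistician blinding is stated and feasible. The claim that a blinded researcher makes all follow-up assessments conflicts with the T3 questions put to one arm.

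On size, awareness of the videos is certain for the experimental mothers (50 pairs planned). The threat to clinical scores through the video questions is confined to T3 and conditional on the examiner asking or hearing them before scoring. The 50 pairs are then an upper limit, not an estimate. No amount of bias can be derived from the document. The sample size and the planned tests are unaffected.

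This rests on two assumptions: that no sham contact exists beyond what the article describes, and that no unseen document already fixes who asks the T3 questions and when. If one does, the order of procedures is settled, but the wording still needs repair.

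**What to change.** 1. Replace double-blind with examiner- and analyst-blinded, participants not blinded, wherever the label appears. Delete the sentence on participants.
2. Limit the blinded-assessor statement in Outcome measurements to the clinical examinations.
3. Have the message sender, who is already unblinded, put the video questions after T3 charting is complete.
4. At each follow-up visit, ask pairs not to mention videos or messages to the examiner.
5. Keep the experimental-only items out of the dataset the statistician uses while blinded.
6. Interpret any self-reported outcome collected after the intervention as open-label.

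Recording the examiner's guess of allocation at T3 would be a useful optional check, but it corrects no error in the text.

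The cost is wording and the order of procedures at visits. No extra staff and no change to sample size are needed. The downside is a less favourable design label.
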